## Abstract

**Background::**

Behcet disease (BD) is a worldwide-occurred autoimmune disorder and currently lack of optional successful treatment. An ancient traditional Chinese medical formula called *Glycyrrhizae* Decoction for Purging Stomach-Fire (GDPSF) was recorded and nowadays has been observed to be effective for BD patients. However, the strict randomized controlled and double-blinding trail is needed to further assess this alternative medicine.

**Methods::**

To ascertain the potential effects and safety of GDPSF for BD patients and to determine whether combination application of GDPSF and thalidomide could possibly reduce the side effects and increase effectiveness for BD management, we will conduct a randomized, double blind, controlled clinical trial. Patients enrolled will be randomly assigned into 3 groups: GDPSF group, thalidomide group, and integrative group (treated by both GDPSF and thalidomide). Participants will receive treatment for 6 months and accept a 12 months follow-up. Before and after treatment, clinical manifestations, blood tests, thalidomide dosage, remission levels, quality of life, and satisfactory levels will be assessed. The data of assessments on each group before and after treatments will be collected and analyzed through historical control, while between groups through intergroup control. Then statistical analysis will be applied to assess the effects and safety.

**Discussion::**

This study protocol will assess the effects and safety of GDPSF for BD patients GDPSF. Combination application of GDPSF and thalidomide might be a new integrative medical method for BD patients.

**Trial registration::**

Chinese Clinical Registry (ChiCTR-ONC-16009621) on Oct. 2016 http://www.chictr.org.cn/showproj.aspx?proj=16395.

## Background

1

Behcet disease (BD) is a type of autoimmune disorder that affects multiple parts of the body. The most common symptoms include painful mouth ulcer, genital ulcer, skin lesions, inflammation of parts of the eye, and arthritis. If the activity of the disease was not been well controlled, the inflammatory reaction may progress to the brain or spinal cord, gastrointestinal tract, blood clots, aneurysms, or blindness. Although the events of vital organs involvement is less frequent but can be life threatening.^[1]^

There is no cure available currently. Treatment is aiming at easing the symptoms, reducing inflammation, and controlling the immune system. Drugs may include immunosuppressive medication such as corticosteroids, colchicine, and thalidomide, etc.^[2]^ However, the quality of the evidence for treating the symptoms such as oral ulcers associated with BD is poor.^[3]^

BD was named after Hulusi Behcet (1889–1948), a Turkish dermatologist in 1937. BD is also known as the name “Silk Road Disease” as it is observed with a higher incidence rate among populations living along the historic Silk Road that from Japan and China in the Far East to the Mediterranean Sea, including countries such as Turkey and Iran.^[4]^ Interestingly, a historical Chinese doctor called Zhang Zhongjing (Chinese: Zhang Zhongjing; 150–219) recorded the similar manifestations as Huhuo disease in his work Synopsis of Golden Chamber, dated from more than 1800 years ago. And the syndrome was treated by *Glycyrrhizae* Decoction for Purging Stomach-Fire (GDPSF, Chinese: Gancao Xiexin Tang).^[5]^ GDPSF is investigated to be effective for BD and many other diseases especially gastrointestinal related.^[6,7]^

GDPSF is a formula comprised of multiple herbs, such as, *Glycyrrhiza uralensis* Fisch, *Panax ginseng* CA Mey, *Scutellaria baicalensis* Georgi, and jujube ect. Due to the complexity of the ingredients, few researches investigated the mechanism of its action. Extractive from *Glycyrrhizae*, which plays sovereign role in the decoction, was reported with antiviral activity^[8]^ while BD is regarded to be induced by various pathogenic microorganisms especially herpes simplex virus-1.^[9]^*P ginseng* has favorable impacts to body metabolism and immune function.^[10,11]^ Massive researches in this way may be considering the underline mechanisms of GDPSFs action.

Some clinical studies published in China reported the effect of GDPSF for BD with high remission rate. However, there have been few high quality trials. There has been no trial that combine GDPSF and chemical drugs as an integrative medical method for BD. This study aims to check the effectiveness and safety of GDPSF in BD patients according to strict, high-quality methodology and follow the Consolidated Standards of Reporting Trails (CONSORT) statement for randomized controlled trials of herbal medicine.^[12]^ The results of this trial hopefully to be published in an authorized publication to be accessed to health providers and BD patients worldwide.

## Methods

2

### Objective

2.1

The primary objective of this study is to ascertain the potential curative or improvement effects and safety of GDPSF for BD patients with mucocutaneous involvement only. The secondary objective is to determine whether combination application of GDPSF and thalidomide could possibly reduce the side effects caused by thalidomide and increase effectiveness for BD management.

### Study design

2.2

This is a single center, double-blinded, randomized, and controlled, parallel-group study. Figure 1 depicts a flow chart of the study. Patients enrolled in this study will randomly be assigned into 3 different groups with respective treatment. Clinical manifestations, blood inflammatory index including erythrocyte sedimentation rate (ESR), C-reactive protein (CRP), and some of the blood biochemical tests will be checked before treatments started (baseline) and will be reexamined on week 4, 8, 12, 18, 20, and 24 during 6 months of treatment to assess the effectiveness and safety. Try to follow up every participant in another 12 months to compare satisfactory rate, complete and partial remission rate, and ineffective rate in different treatment groups.

**Figure 1 F1:**
[figure not shown]
Flow chart of the study. ^1^Integrative group patients receive both thalidomide and Glycyrrhizae Decoction for Purging Stomach-Fire (GDPSF); however, the dosage of thalidomide is range from 25 to 100 mg flexibly according to patients’ treatment sensitivity. ^2^Assessment contents clinical manifestations, blood checkup, and side effects.

### Study population

2.3

This study will be performed in the Rheumatology and Immunology Department of Huadong Hospital affiliated to Fudan University. Patients diagnosed with BD according to the International Criteria for Behcet Disease (ICBD)^[13]^ will be assessed for eligibility. The inclusion and exclusion criteria are presented in Table 1.

**Table 1 T1:**
[figure not shown]
Screening the eligibility of the patients diagnosed with BD.

A patient on admission will receive blood, stool, and urine routine test, ESR, CRP; blood biochemical examination on liver and kidney functions, blood glucose, blood fatty, and electrolytes; coagulation function, autoantibodies, immunoglobulins (Igs), and cancer markers; T-SPORT.TB, hepatitis viruses, HIV, and Treponema pallidum; MRI for skull, X-ray for lung, and ophthalmofundoscope exam; gastrointestinal endoscopy and B-ultrasound for thyroid gland, liver, gallbladder, pancreas, spleen, cardiovascular, urinary, and reproductive systems to screen eligibility of the candidate and record the baseline assessment also.

### Ethical issues

2.4

The trial will be conducted in accordance with the Declaration of Helsinki and the Ethical Guidelines for Clinical Research, and the trial protocol has been approved by the Research Ethical Committee of Huadong Hospital (No: 2014K050). This trial was registered with ISRCTN at Chinese Clinical Registry (ChiCTR-ONC-16009621) on October 2016. Signed consent form will be obtained from BD patients participated prior to randomization.

### Randomization and blinding

2.5

To minimize selection bias, all eligible patients will be randomized in a 1:1:1 ratio to the 3 different intervention groups. Patients will be allocated to each group in turn based on the turn of patients’ identification number generated by Hospital Information System (HIS). Randomization will be performed by a professional, independent statistician who is not involved in the recruitment process of this study. Randomization information will be kept secure in Good Clinical Practice (GCP) Center of Huadong Hospital, neither patients nor doctors know the specific group a participant joined in, and will not be opened until after statistical analysis or in the case of a medical emergency.

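### Section 2.5 claims 1:1:1 randomisation but describes rotation through the groups in hospital-number order, so one leaked assignment exposes other patients and the blind is not protected

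*Protocol article*

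**What the plan says.** Section 2.2 (Study design) declares: "This is a single center, double-blinded, randomized, and controlled, parallel-group study". Section 2.5 (Randomization and blinding) gives the purpose and ratio: "To minimize selection bias, all eligible patients will be randomized in a 1:1:1 ratio to the 3 different intervention groups". Its next sentence gives the mechanism: "Patients will be allocated to each group in turn based on the turn of" the patient number issued by the Hospital Information System (HIS).

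The same section then lists safeguards. On who does it: "Randomization will be performed by a professional, independent statistician who is not involved in the recruitment process of this study". The information is stored at the hospital's GCP Center, and "neither patients nor doctors know the specific group a participant joined in". The code "will not be opened until after statistical analysis or in the case of a medical emergency".

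Two further places bear on the blind. Section 2.6 (Groups and interventions) plans a look-alike pill for the GDPSF group and a look-alike liquid for the thalidomide group. It also fixes thalidomide at 100 mg in the thalidomide group, but lets it range from 25 to 100 mg according to symptom control in the integrative group. The footnote to Figure 1 repeats the flexible range for the integrative group.

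**The concern.** Randomisation protects a comparison because nobody can work out the next assignment from information already available. Going through three groups in the order of an administrative number has no random element. The number order fixes the sequence, whoever applies the rule and wherever the list is kept.

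Two protections are at stake. The first is concealment: a person who has learned the pattern can decide whether to enrol a given patient knowing the group that patient would join. The second is containment of unblinding. Under a random sequence, an opened code exposes mainly the patient concerned. Under rotation it also exposes others, including patients not yet enrolled. The between-group comparisons in section 4.2 rest on this allocation, and no later analysis can restore randomisation that did not take place.

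**Working it through.** **Inputs.** Three groups at 1:1:1 (section 2.5); 150 patients, 50 per group (section 4.1.1, Sample size calculation); allocation by turn in HIS-number order (section 2.5). Assumption: the groups are taken in the same order in every cycle, which is the plain sense of the sentence. The article's own group size is consistent: 3 × 50 = 150. No sample-size figure changes under this point.

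**Step 1: number of possible sequences.** A fixed rotation is determined by which group comes first, second and third: 3! = 6 sequences for the whole trial. Random allocation of 150 patients as 50/50/50 allows 150!/(50!)³ ≈ 2.0 × 10⁶⁹.

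**Step 2: what a leak reveals under rotation.**

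| Known to the guesser (besides the number order) | Assignments settled | Expected share guessed correctly |
|---|---|---|
| Nothing | 0 of 150 | 1/3 = 33% |
| One patient's group | 50 of 150 (that patient included) | (50 + 100 × 0.5)/150 = 67% |
| Two patients from different groups | 150 of 150 | 100% |

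In the second row two arrangements remain for the other 100 patients, so a guess is right for all of them or for none. The average is 50 of the 100.

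**Step 3: comparison with real randomisation.** Give the guesser every past assignment and always guess the group with fewest patients so far. In 300 simulated lists of 150 for each method, the guess was right about 34% of the time under simple randomisation and about 54% under permuted blocks of 6 or 9. Under rotation, a guesser who knows the rule and every past assignment has a 1/3 chance for the first patient, 1/2 for the second and certainty afterwards: (1/3 + 1/2 + 148)/150 = 99.2%.

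**Step 4: the other literal reading.** If the turn meant the remainder of the HIS number on division by 3, the number alone would still determine the group. With remainders equally likely, an exact 50/50/50 split would have probability 2.0 × 10⁶⁹/3¹⁵⁰ ≈ 0.5%. That reading is no more random, and it fits the stated group sizes poorly.

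**Step 5: can the key be learned?** The article itself provides two routes. Section 2.5 allows the code to be opened in an emergency. Section 2.6 describes response-based thalidomide dosing for the integrative group only, so a dose change visible to a treating doctor points to that group, which by Step 2 settles 50 assignments. How that dosing fits with the double-blind claim must be reconciled; no dosing rule is suggested here.

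**The case against.** **The safeguards and the milder reading.** An independent statistician and secret allocation information would have little purpose under bare rotation. Perhaps the statistician holds a random list, patients take the next slot in number order, and a condensed article has worded this badly. That is possible, but the article does not say so, and its sentence has patients going to each group in turn. Even on this reading the sentence misdescribes the trial and must be corrected. This is also not detail left to a fuller document: the article states a method, and the method conflicts with its own claim.

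Four stronger readings are tempting, and the document does not support them:

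- *The blind has failed.* Rotation alone unmasks nobody. Look-alike placebos are planned, and which position belongs to which group must first be learned.
- *The next assignment is always certain.* That holds only for someone who knows the rule, the order and the key. Without the key the chance is 1 in 3, the same as under simple randomisation.
- *Recruiting doctors see the order.* The article says only that HIS generates the number. It does not say who sees the enrolment order, or whether the number is issued at hospital registration or at trial entry. If at registration, delaying enrolment would not change the number, though withholding enrolment would remain possible.
- *The trial can never be reported as randomised.* The text supports a contradiction that must be resolved. It does not show what was actually done.

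Emergency opening of the code is an ordinary safety provision and no defect in itself. It matters here only because rotation spreads its effect to other patients.

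**Conclusion.** The point holds. Section 2.5 claims randomisation and then states a deterministic rule, and its other safeguards do not make that rule random. If followed as written, the allocation is one of 6 sequences; a single identified patient settles 50 of 150 assignments, and two from different groups settle all 150. Concealment and blinding then depend entirely on the position-to-group key never leaking, while the document itself contains routes by which it could. The right description is that the blind is not protected.

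These counts assume the same group order in every cycle and a guesser who knows the rule and can place patients in number order. The effect on a remission difference cannot be sized from the document, which gives no basis for how many patients might be selectively enrolled or how their prognosis would differ. The sentence should be corrected before the between-group results are relied on.

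**What to change.** Delete the in-turn sentence and state instead:

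- The independent statistician generates by computer a 1:1:1 random sequence in permuted blocks of varying size. The sizes are not disclosed to anyone involved in recruitment or care.
- HIS numbers identify patients only and play no part in allocation.
- The GCP Center holds the list. Each assignment is released by a central or pharmacy code, and only after consent and eligibility have been recorded.

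Coded release suits this trial because the decoction is prepared in the hospital's own dispensary.

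If such a list already exists, correct the sentence to describe it. Separately, reconcile the flexible dosing text in section 2.6 and Figure 1 with the double-blind claim.

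The cost is small: protocol wording, one generated list and a coded release step through the dispensary. The statistician and the GCP Center are already in place, and the sample size does not change.

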### Groups and interventions

2.6

Included patients will be randomly allocated into 3 groups: GDPSF group, thalidomide group, and integrative group. GDPSF group will receive GDPSF and placebo pills of thalidomide size, color, and shape made from cheese. Thalidomide group will take 100 mg thalidomide pill every night and placebo water of GDPSF color and amount. Integrative group will receive both GDPSF and thalidomide, which dosage could be flexible, range from 25 to 100 mg as long as the symptoms could be controlled during the treatment period. All of the patients in these 3 groups will take their medications for 6 months duration.

GDPSF composed of 7 herbs, including 12 g *Glycyrrhiza uralensis* (GanCao), 9 g *Scutellaria baicalensis* (HuangQin), 12 g *Pinellia ternate* (BanXia), 3 g *Coptis chinensis* (HuangLian), 9 g *Zingiber officinale* (GanJiang), 9 g *P ginseng* (RenSheng), and 12 piece of Jujube (HongZhao). The components of formula will be decocted in Herbs Dispensary of our hospital by herbs tisanes machine, into 3 sealed bags of liquid, 200 mL for each bag. Patients can save the herbal decoction in refrigerator and warm it in microwave oven before taken.

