### Primary outcome measures

3.1

As the oral and genital ulceration, skin lesions (erythema nodosum) are most common complaints in BD patients. We select a mucocutaneous activity index (MAI) in BD created by Mumcu et al.^[14]^ In this MAI:Presence of the lesion was coded as 1 for actives and 0 for inactives (0 vs 1 point)Pain was evaluated by 100 mm-visual analogue scale (VAS; 0: no pain–100: severe pain) by patients. Then, the VAS score was categorized to calculate the score as follows: ≤10: 0; 11–20: 1; 21–40: 2; 41–60: 3; 61–80: 4; 81 and over: 5 points.Functional status was evaluated by a 5-point Likert-type scale: none of the time (0 points), little of the time: 1 point, some of the time: 2 points, most of the time: 3 points and all of the time: 4 points. Mean score was used in the index (Table 2).

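### The dummy thalidomide pill is specified as cheese and matched only on visual features, which weakens the claimed double blind for the GDPSF group

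*Protocol article*

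**What the plan says.** Study design (2.2) makes the masking claim: "This is a single center, double-blinded, randomized, and controlled, parallel-group study". Randomization and blinding (2.5) adds that "neither patients nor doctors know the specific group a participant joined in".

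Groups and interventions (2.6) describes what each group takes:

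- GDPSF group: the real decoction and "placebo pills of thalidomide size, color, and shape made from cheese".
- Thalidomide group: "Thalidomide group will take 100 mg thalidomide pill every night and placebo water of GDPSF color and amount".
- Integrative group: "Integrative group will receive both GDPSF and thalidomide, which dosage could be flexible, range from 25 to 100 mg".

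On duration, the same section says: "All of the patients in these 3 groups will take their medications for 6 months duration". Its storage advice concerns the decoction only.

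Under Primary outcome measures (3.1), the MAI includes a pain item that patients score themselves: "Pain was evaluated by 100 mm-visual analogue scale". Under Secondary outcome measures (3.2), satisfaction is also the patient's own judgement.

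**The concern.** A double-dummy design masks only as well as its dummies. Here the material of one dummy is stated, and it is a food. Size, colour and shape govern what a patient sees; they do nothing about what a patient tastes or smells. Someone who takes such a pill repeatedly over the treatment course has many chances to notice what it is.

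Recognition would be fully informative. No other group receives a dummy pill, so identifying it as food identifies the GDPSF assignment. GDPSF is also the subject of the primary objective (2.1). If some of these patients know their group, self-rated pain and satisfaction may reflect belief about treatment as well as its effect, and the analysis could not separate the two.

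**Working it through.** There is no figure in the plan to reproduce. The check sets out the products by group and asks which dummy carries the blind in each contrast.

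**Products by group (2.6)**

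| Group | Liquid | Pill |
|---|---|---|
| GDPSF | active decoction | dummy (cheese) |
| Thalidomide | dummy (coloured water) | active |
| Integrative | active decoction | active |

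**What separates each pair**

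| Contrast | Liquid differs? | Pill differs? | Blind rests on |
|---|---|---|---|
| GDPSF v integrative | no | yes | pill dummy alone |
| GDPSF v thalidomide | yes | yes | both dummies |
| Integrative v thalidomide | no dummy pill; liquid differs | both active | liquid dummy alone |

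The dummy pill therefore bears on two of the three contrasts and is the only dummy in one of them.

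**Who is exposed.** Sample size calculation (4.1.1) plans 50 patients per group and 150 in total. The dummy pill goes to 50 / 150 = one third of them. These are the patients who could recognise it; how many would do so is unknown.

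**What recognition reveals.** The trial is parallel-group, so a patient normally holds one pill type. The route to unmasking is recognising the food itself. No second pill is needed for that, because a dummy pill occurs in one group only.

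**Which outcomes are exposed.** By the scoring in 3.1, lesion presence gives 0 to 1 point, pain 0 to 5 and functional status 0 to 4. Pain is explicitly scored by the patient. Function uses a Likert-type scale, and the text does not say who completes it. Table 2, which sets out the index and its subscales, is not shown, so the patient-rated share of the total MAI cannot be worked out. It can be said that the pain item spans more points than lesion presence (5 against 1). Satisfaction (3.2) is wholly patient-rated.

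**Against the blinding claim.** Sections 2.2 and 2.5 claim masking of patients and doctors without qualification. Section 2.6 names a dummy material with its own taste and smell and lists no matching on either. The two sit poorly together.

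**The case against.** The strongest reply is that only the word for the material is firm. An article need not list coating, taste matching, packaging or shelf life, and silence on those is no fault. A coated pill swallowed whole might mask well enough. The English is loose in places, so the word may be a slip. All of this is fair, and it limits the point to what is stated. But the material is stated, nothing in the article corrects it, and a slip would still need correcting.

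Several stronger readings are tempting and are not supported:

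- **Comparing pills.** A reader might infer that patients would compare active and dummy pills. The parallel design makes this unlikely.
- **Spoilage over 6 months.** A reader might infer that the pill would visibly age. No dispensing interval or shelf life is given, and Statistical analysis (4.2) has visits every 4 weeks, so long storage is not established.
- **A numerical bias.** One might assume a pain shift of 10 to 20 mm and convert it to about one pain category. Nothing in the document supports that shift. In the 20 mm bands with evenly spread scores, a 10 mm shift would cross a boundary for only 10 / 20 = half of patients.
- **Direction and dropout.** One might expect bias towards the integrative group and more dropout on GDPSF. Patients who prefer herbs or fear thalidomide could respond the other way.
- **GDPSF versus integrative as the key contrast.** Section 4.1.1 names thalidomide alone as the comparator of interest, for GDPSF and for the combination. The combination-versus-thalidomide comparison does not involve the dummy pill.

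It also stands that a better dummy would not secure the blind. Safety assessment (4) lists noticeable thalidomide effects such as numbness and constipation. Section 2.6 lets the integrative dose vary and states no parallel adjustment of the dummy. Either could unmask the same groups. That limits the benefit of the fix but does not justify a recognisable dummy.

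**Conclusion.** The point holds in a limited form. The stated pill material is a weak basis for the double blind that the article claims. The weakness is greatest for GDPSF versus integrative, where the pill is the only dummy; in GDPSF versus thalidomide it adds to whatever the liquid dummy leaves unmasked. It reaches the planned 50 GDPSF patients and mainly threatens patient-rated pain and satisfaction.

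The size and direction of any bias are unknown. The conclusion assumes that the word means what it says and that no coating or capsule, unmentioned in the article, hides taste and smell. It does not show that patients will be unmasked. It is worth acting on before treatment starts, because a lost blind cannot be restored afterwards.

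**What to change.** 1. Replace cheese with an inert, odourless pharmaceutical excipient, or encapsulate active and dummy pills identically, so that taste and smell match as well as appearance. If the word is a translation error, correct it and state the true composition.
2. At week 24, already an examination time in 2.2, ask each patient which treatment they believe they received, and report the answers by group. Read them with care: guesses can reflect efficacy or side effects as well as the pill.

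The cost is a change of excipient or an encapsulation step, judged to be small although the document gives no cost figures, plus one question. No patients or visits are added. Encapsulation would have to cover every form in which active thalidomide is dispensed. The change does not remove unmasking through thalidomide side effects or the flexible dose in the integrative group; the report should say so.

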**Figure 2 F2:**
[figure not shown]
Patients general satisfaction to the treatment.

Dosage of thalidomide in patients of integrative group will be recorded. This will to evaluate when combination application with GDPSF, if dosage of thalidomide dosage could be decreased.

Quality of life for BD: The quality of life BD, developed by Gill Gilworth et al, provides us with a simple, reliable, and valid tool for assessing the influence of interventions for BD and for evaluating models of service delivery.^[15]^ It is well accepted by patients and has scaling and psychometric properties.

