#### Sample size calculation

4.1.1

One of the aim in the study aims to detect the symptoms easing effect of GDPSF in BD through historical control. The complete remission of symptoms rate reported ranged from 22% to 81%, while effective rate generally above 70%.^[17]^ The reported complete remission rate of thalidomide for BD symptoms ranges from 6% to 81%.^[18,19]^ We also interested in the effects of GDPSF or its combination application with thalidomide compared with thalidomide alone, especially on whether GDPSF improved outcomes or reduce thalidomide intake and its side effects.

Since no strict randomized controlled trials have been previously performed, we proposed this study to evaluate the feasibility of a large-scale clinical trial. Anticipating a 20% dropout rate, a total of 150 patients, with 50 patients in each group, will be recruited for this pilot study.

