### Statistical analysis

4.2

This is an 18 months clinical trial, in which participants will receive treatment for 6 months and accept a 12 months follow-up. During their treatment, participants will visit investigators every 4 weeks 5 times in all. Their clinical manifestations (MAI), blood tests, thalidomide dosage in thalidomide, and integrative groups will be assessed. Participants will receive 2 times of follow-up for 12 months after treatment, their remission levels, quality of life, and satisfactory levels will be assessed. Figure 3 summarizes the study schedule of enrollment, interventions, and assessments according to the SPIRIT 2013 statement. The data of assessments on each intervention group before and after treatments will be collected and analyzed through historical control, while between groups through intergroup control method.

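### Only the integrative group may lower its thalidomide dose, so lower intake or fewer thalidomide side effects cannot be attributed to GDPSF

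*Protocol article*

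**What the plan says.** Section 2.6 (Groups and interventions) fixes the comparator: "Thalidomide group will take 100 mg thalidomide pill every night", with a liquid placebo for the decoction. For the combination it says: "Integrative group will receive both GDPSF and thalidomide, which dosage could be flexible, range from 25 to 100 mg", and the condition is "as long as the symptoms could be controlled during the treatment period". The Figure 1 legend repeats the rule for the integrative group alone: "the dosage of thalidomide is range from 25 to 100 mg flexibly according to" the patient's sensitivity to treatment. No titration is described for the thalidomide group.

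Three places give the purpose of the dose and side-effect data:

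- Section 3.2 records the integrative group's dose and explains: "This will to evaluate when combination application with GDPSF, if dosage of thalidomide dosage could be decreased".
- Section 4.1.1 states the interest as "especially on whether GDPSF improved outcomes or reduce thalidomide intake and its side effects".
- The Discussion hypothesises that the formula may reduce events such as leukopenia and peripheral neuropathy caused by thalidomide, and gives this as the reason for having an integrative group.

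Section 4.2 adds that "thalidomide dosage in thalidomide, and integrative groups will be assessed", and that data are compared "while between groups through intergroup control method". Its tests are generic: ANOVA or t test, otherwise Kruskal–Wallis, and chi-squared for counts, at P < .05. No between-group test of dose is singled out.

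**The concern.** To say that GDPSF spares thalidomide, one must know what dose similar patients would have needed without GDPSF. The thalidomide group could supply that information only if its dose were free to fall under the same rule. It is held at 100 mg, which is also the top of the integrative range, so a patient on thalidomide alone who would have been controlled on 50 mg is still prescribed 100 mg.

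The side-effect comparison has the same weakness. If the integrative group has less neuropathy or leukopenia, lower exposure is a sufficient explanation and GDPSF need have done nothing.

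Section 4.1.1 describes the study as a pilot for a large-scale trial. A dose-saving signal produced by the dosing rule could be carried into that trial as an effect of the herbal formula.

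**Working it through.** **1. What is wanted and what is observed.** For a given patient, let D0 be the lowest controlling dose without GDPSF and D1 the lowest controlling dose with it, both between 25 and 100 mg. The effect of interest is the mean of D0 − D1. If titration finds D1, the prescribed doses give the mean of 100 − D1, which splits as

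100 − D1 = (100 − D0) + (D0 − D1).

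The first bracket is never negative and comes from the dosing rule alone. Only the second belongs to GDPSF. D0 is observed in nobody, because the thalidomide group is not titrated, so no analysis of these data can separate the two brackets.

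**2. Bounds.** If every integrative patient is prescribed 25 mg throughout, the mean difference is 100 − 25 = 75 mg, or 75%. If all need 100 mg, it is 0. This concerns the prescribed dose.

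**3. Dose test with an inert GDPSF (illustration).** Inputs from section 4.1.1 are 50 per group and 20% dropout, giving 50 × 0.8 = 40 completers. Assumptions: every thalidomide patient analysed takes 100 mg, k integrative patients take less, and the generic Kruskal–Wallis test is applied to dose.

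| k of 40 below 100 mg | asymptotic p | exact two-sided p |
|---|---|---|
| 3 | 0.079 | – |
| 4 | 0.041 | 0.116 |
| 5 | 0.022 | 0.055 |
| 6 | 0.011 | 0.026 |

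The exact value is 2 × C(40,k)/C(80,k); for k = 6 this is 2 × 3,838,380/300,500,200 = 0.026. Significance needs k ≥ 4 (asymptotic) or k ≥ 6 (exact). The size of the reduction hardly matters: four patients at 75 mg give a mean difference of 4 × 25/40 = 2.5 mg and still p = 0.041 asymptotically.

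With 50 per group the thresholds remain 4 (p = 0.042) and 6 (p = 0.027). Taking k as binomial, with an assumed share of patients who would be controlled below 100 mg anyway, the chance of a significant dose saving is:

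| Assumed share | 40, asymptotic | 40, exact | 50, asymptotic | 50, exact |
|---|---|---|---|---|
| 0% | 0% | 0% | 0% | 0% |
| 5% | 14% | 1% | 24% | 4% |
| 10% | 58% | 21% | 75% | 38% |
| 20% | 97% | 84% | 99% | 95% |

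The article gives no such share and does not say whether the test is asymptotic or exact.

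**4. Side effects with an inert GDPSF (illustration).** Assume event risk rises linearly from 10% at 0 mg to 40% at 100 mg, so risk = 0.10 + 0.30 × dose/100. Assume also that 25/50/75/100 mg is the lowest controlling dose in the proportions shown. The thalidomide group's risk is 40%. The last column is simulated, with 40 per group and an uncorrected chi-squared test.

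| Proportions (%) | Mean integrative dose | Integrative risk | Chance of a significant reduction |
|---|---|---|---|
| 10/10/10/70 | 85 mg | 35.5% | about 7% |
| 25/25/25/25 | 62.5 mg | 28.8% | about 19% |
| 70/10/10/10 | 40 mg | 22.0% | about 41% |

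The dose-response and the proportions are assumed. The table shows the mechanism and does not estimate its size in this trial.

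**The case against.** The strongest reply is that a flexible-dose combination against a standard fixed dose is a legitimate pragmatic comparison. Section 2.1 asks about the combination, and the design answers that. The section 4.1.1 sentence opens with GDPSF or its combination compared with thalidomide alone, so part of it can be read the same way. The Discussion offers a hypothesis and specifies no test, and the study calls itself a pilot. All of this stands and limits the point to attribution. It does not remove the point, because the end of that sentence makes GDPSF itself the agent that lowers intake and side effects, section 3.2 ties the lower dose to GDPSF, and the Discussion does so for side effects.

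It is also fair that the plan does not single out a between-group dose test and that the probabilities above depend on an assumed share. They are illustrations. The confounding is present even if the doses are only described.

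A reader might infer three stronger things that the article does not support:

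- **That the dose actually taken can only favour the combination.** Under section 4 (Safety assessment), patients with serious adverse events stop the medicine, so intake in the thalidomide group can fall below the prescribed 100 mg. The one-directional statement holds for prescribed dose only.
- **That titrating one group breaks the blind claimed in section 2.5.** Who sets the dose is operational detail that a condensed article may leave to the full protocol. Allocation is held by a separate centre, so a dose-setter outside the blinded team is compatible with the text.
- **That the efficacy comparisons are compromised.** GDPSF versus thalidomide involves no titration, and permission to use less thalidomide does not explain better symptom control with the combination.

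**Conclusion.** The point holds for two secondary conclusions: that GDPSF reduces thalidomide intake, and that GDPSF reduces thalidomide side effects. The dosing rule alone can produce both, and the data cannot separate its contribution from that of GDPSF. This follows from the dosing stated in section 2.6 and needs no numerical assumption.

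The direction of the prescribed-dose difference is fixed, and its mean lies between 0 and 75 mg. How often an inert GDPSF would appear to save dose cannot be determined from the article. Over assumed shares of 0% to 20% the illustration runs from 0% to 99%, and it presumes full 100 mg intake in the thalidomide group and use of the generic test on dose. It should be corrected before reporting.

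**What to change.** Report integrative versus thalidomide as a comparison of two regimens: GDPSF plus flexible thalidomide (25–100 mg) versus fixed 100 mg. Keep the section 2.1 objective in that sense. Summarise the integrative dose descriptively, with no between-group test against the fixed 100 mg. In sections 3.2 and 4.1.1 and the Discussion, remove the attribution of dose saving and side-effect reduction to GDPSF.

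The cost is limited to text and reporting. No patients, visits or procedures are added, and a secondary conclusion credited to GDPSF is given up.

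If that attribution is itself wanted, both thalidomide-containing groups need the same masked titration rule, with dummy dose changes in the GDPSF group. That requires an amendment and masked dose steps, and it replaces the fixed 100 mg comparator in the GDPSF-versus-thalidomide contrast with a titrated one. It is a design trade-off and is not needed to correct the present text.
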